**Fig. 3 Fig3:**
[figure not shown]
Flow chart of study participants

Home visits will be made for participants missing clinic visits while those coming to their scheduled clinic visits will have the transport fees reimbursed to reduce losses to follow-up. Data on illness, hospital visits and hospitalization is collected from interviews with the mother, with more detailed information obtained from the hospital records. Illness and hospitalization data is based on recall between a previous visit and a current visit.

Upon enrollment and on subsequent visits, mothers and other caregivers are informed about symptoms and signs of severe illness, and are encouraged to contact the study clinic in case the baby develops any of these symptoms. Each mother is provided with a durable note book, in which she is instructed and trained to note down all relevant events in her child. The front page of the book will have clear reminders that she needs to contact the study team in case the child visits a health clinic, a physician or is admitted to a hospital. A child who comes to a clinic with such symptoms is examined by a study nurse/midwife. If the child does not attend after the mother/caregiver has informed the study team of such signs or for a scheduled visit, the study nurse/midwife will make a visit to the child’s house. If the nurse/midwife classifies the condition as possible severe illness, a study physician will be called to examine the child. If the physician classifies the child as having severe illness, they will collect a blood specimen for blood culture (using BACTEC) and a sepsis screen (CRP, TLC, differential count, and band cell:neutrophil count ratio) as soon as possible. A repeat specimen will be collected again for CRP between 24 and 48 h. The study team will do its utmost to obtain specimens for such a sepsis screen from as many infants with signs of severe illness as possible. However, we have yet to learn what percentage of them in this way can actually be screened for “clinical sepsis.” When 200 enrolled babies have been followed until the age of 6 months, the percentage of infants registered as having had severe illness who are screened for clinical sepsis will be calculated. If this percentage is less than 80%, measures will be taken to increase it above this value, if these measures are unsuccessful, we will need to abandon the attempt to identify clinical sepsis with the sepsis screen. Length and weight measurements are taken twice at each visit, based on the WHO guidelines, and z-scores calculated using WHO child growth standards [68].

## Data collection and management

All trial procedures have been standardized. Training exercises were undertaken and refresher sessions are scheduled during the trial. Using Open Data Kit (ODK, https://opendatakit.org), we will use pre-coded electronic Case Report Forms (eCRFs)/questionnaires with range and consistency checks. Entered data will be checked for consistency and any errors corrected

Source documents and files will not be destroyed without specific written permission from the PI. Only the PI, Co-PI, study coordinator and authorized study personnel will have access to the CRFs and supporting documents that will be kept on password-secured computers to ensure participant confidentiality. To ensure correct operation according to standard operating procedures (SOPs) all system users have been trained in their use and evaluated on a regular basis.

## Clinical laboratory tests

Heel-prick blood samples are obtained from the children for HIV-1 diagnosis. Dried blood spots (DBS) using a commercial PCR kit are used for HIV-1 diagnosis. This testing is supported by standardized protocols that have been successfully validated in Uganda. Flow cytometry is used for CD4 count measurement while standardized automated procedures and techniques are used for hematological and biochemical plasma assays. ELISA and/or rapid tests are used for maternal HIV-1 diagnosis according to the Ugandan national guidelines. At week 14 and week 52, blood will be drawn by venipuncture for full/complete blood counts. TLC, differential count and CRP will be captured as part of the sepsis screen in babies with clinical severe illness.

## Functional immunology assessment

We will investigate both the induction of trained immunity and heterologous immunity. Blood cells will be stimulated for 48 h with a lysate of BCG or *M. tuberculosis*, and IFN-γ production will be measured by ELISA as a measure of classical adaptive immunity. Using the cell culture medium (RPMI) as a control stimulus, trained innate immunity will be assessed by stimulation of blood for 24 h by unrelated nonspecific stimuli: lipopolysaccharide (LPS), heat-killed *E. coli*, *C. albicans* or *S. aureus* at 1, 15 and 28 weeks of age. Production of the monocyte-derived cytokines TNF, IL-1β and IL-6 will be assessed by ELISA. Genome-wide gene transcription will be assessed in the unstimulated and stimulated whole blood by ribonucleic acid (RNA) sequencing. Heterologous immunity will be assessed by measurement of both Th1 (IFN-γ) and Th17 (IL-17, IL-22) cytokines in blood stimulated for 96 h with the nonspecific stimuli described above. The anti-inflammatory cytokine IL-10 will also be assessed at the 48-h stimulation time point. Protein and messenger ribonucleic acid (mRNA) assessment will be our main immunological readouts.

## Quality assurance and quality control

We will use the WHO Good Laboratory Practice Guidelines [69] as our reference when establishing quality control laboratory procedures. HIV-1 serology, CD4 counts, hematology/biochemistry and immunology assays are submitted to a stringent quality assessment programme. On-going training and monitoring will occur during the study.

## Handling losses, withdrawals and protocol deviations

### Protocol deviations

If a protocol violation, such as an inadequate informed consent, inappropriate randomization or concealment or wrongful enrollment of an under-age mother occurs, the PI will inform the Independent Data Monitoring Committee (IDMC), which consists of a pediatrician, a statistician and a pediatrician/immunologist), the Project Management Team (PMT, which consists of some of the authors of this paper) and the local Ethical Committee as soon as possible and no later than five working days after the event. Detailed documentation mentioning the dates and reasons of these protocol deviations will be kept by the PI. If continuing the child in the trial puts the health of the mother or her child at risk, the child will no longer be followed up, but their data will be included in time-to-event analyses up to the time that they were removed from the trial.

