## Trial size estimates for the primary hypotheses

### Hypothesis A

The outcome in this hypothesis is severe illness in the first 14 weeks of life. Based on an estimated 10% risk of severe illness in the first 14 weeks of life [65], 90% power and a risk ratio of 0.7, the required sample size is 1914 (Table 1).

**Table 1 Tab1:** Assumptions used for sample size calculation for the first 14 weeks of life

Assumption	Estimated level
Two-sided significance level	0.05
Ratio of sample size early/late BCG vaccination	1
Percent of vaccinated at 14 weeks of age with severe illness	15
Percent of vaccinated at birth with severe illness	10
Risk ratio:	0.7
Risk difference	5
Total sample size (i.e., in both trial arms)	1914

*BCG* Bacillus Calmette-Guérin

Taking into account 10% attrition and that up to 5% of the infants may have contracted HIV-1 infection when enrolled, a total of 2200 babies are required for this trial, 1100 children in each study arm.

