### Primary analysis

The main study outcomes are severe illness during the first 14 weeks of life and immunological parameters. Although the sample size estimations are based on specified relative risks, i.e., the occurrence of one or more illness episodes per child, our final analysis will also use incidence density and use Poisson regression or, in case of overdispersion, negative binomial regression analyses, to estimate incidence rate ratios (IRR), enabling us to capture more than one illness event in each child. Further, children who are lost to follow-up will be included in time-to-event analyses, censoring children during periods when data could not be recorded. All randomized children will be included in an *intention-to-treat* analysis.

To take into account multiple study events occurring in the same child, we will in the regression models utilize generalized estimating equations (GEE), as appropriate. The effect of the intervention on the occurrence of severe illness will be estimated using both relative (relative risks (RR), IRR and hazard ratios (HR)) and absolute (risk differences and incidence rate differences (IRD)) measures of effect. In the event that the “relative risk regression” model fails to converge, risk ratios will be obtained from logistic regression [70] or from a modified Poisson regression model with robust variance [71, 72].

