Also, autoregressive correlation approaches will be used to account for multiple and possibly correlated observations within the same study participant. These methods take the correlation structures into account and thereby the fact that measurements taken closer in time for an individual are likely to be more correlated than two measurements taken farther apart for that same individual. Efficacy will be calculated as 100 × (1 − RR), 100 × (1 − IRR) or 100 × (1 − HR). The prevalence of BCG scarring will be compared between the two study arms using the abovementioned approaches, as appropriate. Linear regression and or *t* tests will be used to compare the TNF and IFN-γ responses between the trial arms. We will consider adjusting for potential confounders if: (1) there are baseline imbalances between trial arms, (2) the variables for which there are such baseline differences are strongly associated with the study event or (3) they cause a ≥5% difference in the effect measures when they are added to the main model. Full case analyses will be default, but appropriate imputations will be considered for missing data.

In addition to the *intention-to-treat analysis*, where outcomes will be compared according to the random allocation, *instrumental variable analyses* will be conducted in an attempt to estimate biological/causal effects of the actual receipt of the vaccine. In these analyses, random allocation will be the instrument. To enable such analyses, actual receipt as well as the age of BCG vaccination will be captured in all participants. We will also perform *per-protocol* and *as-treated* analyses.

The primary analyses will include all HIV-1-exposed infants, adjusting for any imbalance in HIV-1 status between the two trial arms, as appropriate. However, we will also perform an analysis of the large subgroup of babies who remain uninfected with HIV-1.

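### Removing a child on health grounds also ends outcome follow-up; with a full-case default, such children leave the 14-week risk ratio despite the intention-to-treat promise

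*Protocol article*

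**What the plan says.** Four statements in the protocol article bear on this.

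- **Protocol deviations.** After examples such as inadequate consent, faulty randomization and under-age enrolment, the section turns to cases where staying in the trial endangers the health of mother or infant: "the child will no longer be followed up, but their data will be included in time-to-event analyses up to the time" of removal. No other use of these data is mentioned.
- **Primary analysis, population.** "All randomized children will be included in an" intention-to-treat analysis, later described as a comparison by random allocation. For losses, "children who are lost to follow-up will be included in time-to-event analyses, censoring children during periods when data could not be recorded".
- **Primary analysis, measures and missing data.** For severe illness, the effect of vaccination timing "will be estimated using both relative (relative risks (RR), IRR and hazard ratios (HR)) and absolute (risk differences and incidence rate differences (IRD)) measures". On missing data: "Full case analyses will be default, but appropriate imputations will be considered for missing data".
- **Hypothesis A.** The trial is sized on a risk ratio for severe illness by 14 weeks, and the total is raised to 2200 "Taking into account 10% attrition" and up to 5% HIV-1 infection at enrolment.

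**The concern.** Time-to-event and rate analyses can use a child up to the day of removal. A 14-week risk ratio or risk difference cannot do so without a further rule: an infant who leaves event-free at week 5 has no known status at week 14. The deviation clause stops outcome collection and keeps the child only for time-to-event analyses. The missing-data default then drops the child from the risk comparison. For the measure on which the trial was sized, these rules and the promise to include all randomized children cannot all hold.

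Two features make the loss more than administrative. The ground for removal is health, so removed children may differ in risk from those who stay. And the trial is open label (Blinding/masking), so a judgement that participation is a risk can depend on the arm. The Ethical considerations section lists three main concerns, each attached to one arm: TB before protection (delayed), severe BCG disease in HIV-1-positive infants (early), and more severe illness in the first 14 weeks (delayed). Removal related to both arm and outcome would bias the risk ratio in a direction not known in advance. The clause also cuts off the secondary outcomes collected to week 52: death, adverse events and growth.

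**Working it through.** **1. The plan's own figure.** Inputs from Table 1: risks of 15% (delayed) and 10% (birth), two-sided 0.05, 1:1 allocation; power of 90% from the text of Hypothesis A. The continuity-corrected two-proportion formula gives 957 per arm, or 1914 in total, exactly as stated. Inflation: 1914 × 1.15 = 2201, against the stated 2200. The base-case risk ratio is 10/15 = 0.667 (printed as 0.7). With all 2200 followed, power is 94.4% (uncorrected formula).

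**2. Model for removal.** Let p be the arm's true 14-week risk, f the share removed event-free before week 14, and k the risk in removed children relative to the arm average. The full-case risk is

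p × (1 − f·k) / (1 − f).

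The documents give neither f nor k. The values below are assumptions: k = 2 to 3, with f varied.

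**3. Example.** With 1% removed in the birth arm, 2% in the delayed arm and k = 2: birth 0.10 × (1 − 0.02)/0.99 = 0.0990; delayed 0.15 × (1 − 0.04)/0.98 = 0.1469; risk ratio 0.674.

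**4. Range** (true risk ratio 0.667).

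| Removed, birth / delayed | RR, k = 2 | RR, k = 3 | Power, k = 2 / k = 3 |
|---|---|---|---|
| 1% / 1% | 0.667 | 0.667 | 94.0% / 93.7% |
| 10% / 10% | 0.667 | 0.667 | 88.3% / 83.2% |
| 1% / 2% | 0.674 | 0.681 | 92.5% / 90.7% |
| 0% / 2% | 0.681 | 0.695 | 91.5% / 87.9% |
| 2% / 0% | 0.653 | 0.639 | 95.8% / 97.1% |
| 0% / 5% | 0.704 | 0.745 | 84.9% / 69.4% |

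Equal, equally informative removal leaves the risk ratio alone but understates both risks: at 10% removed, 15%/10% becomes 13.3%/8.9% (k = 2) or 11.7%/7.8% (k = 3).

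**5. No true effect, 2% removed in one arm only.** The risk ratio becomes (1 − 0.02k)/0.98, which is 0.98 for k = 2 and 0.96 for k = 3.

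**6. Ordinary attrition.** The same default applies to the planned 10%, at most 0.10 × 2200 = 220 infants. Equal loss rates do not guarantee safety. If 10% are lost in each arm but carry twice the average risk in one arm only, that arm's risk is multiplied by (1 − 0.2)/0.9 = 0.889, and a null risk ratio becomes 0.89 or 1.13. The 220 is a ceiling: it assumes that all attrition occurs event-free before week 14.

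**The case against.** A reader might infer that the plan drops the sickest infants. The documents do not support that. The trigger is danger from continuing in the trial, to mother or child, and it sits in a section about violations. Severe illness is not named as a reason for removal. The Follow-up section has suspected severe illness examined, with a home visit if the child does not attend, and serious adverse events are followed to resolution or a stable endpoint. The arm-specific concerns under Ethical considerations are met by screening, referral and treatment, with no mention of removal. So the link between removal and outcome is possible but not stated. This part of the objection stands.

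A reader might also infer that intention-to-treat is contradicted outright. For the hazard ratio and incidence rate ratio it is not: censored children contribute time in their allocated arm, and events before removal count. What remains there is the assumption of non-informative censoring. The conflict is confined to the risk ratio and risk difference.

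The full-case sentence follows the rule on covariate adjustment and may concern covariates only. The same sentence leaves imputation open, and detail on imputation properly belongs in an analysis plan that is not shown. This weakens the point but does not remove it. The article itself fixes the end of follow-up, and no later analysis plan can recover outcomes that were never collected. Follow-up of an existing serious adverse event also does not cover a later illness or death.

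**Conclusion.** The point holds as a cheap improvement. The article ends outcome follow-up for children removed on health grounds and keeps their data only in time-to-event analyses. Read with the full-case default, that takes infants removed or lost event-free before week 14 out of the 14-week risk ratio and risk difference, against the statement that all randomized children are included.

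The effect of removals is probably small: about 0.01–0.04 on the risk ratio at 1–2% removal with removed children at 2–3 times average risk, and none if removal is equal and equally informative in both arms. These figures rest on assumed removal rates and risks. Larger shifts need larger one-sided removal, such as 5% of one arm (55 of 1100 infants), for which nothing in the documents gives grounds. Assuming that every removed child would have fallen ill, all in one arm, would give a much larger bias: at a 12.5% risk and 2% removed, ((0.125 − 0.02)/0.98)/0.125 = 0.86 instead of 1.00. A reader might reach for that figure, but it gives removed children eight times the average risk, which the documents do not support.

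**What to change.** Reconcile the Protocol deviations and Primary analysis sections:

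1. **Separate the two kinds of stopping.** State that removal ends trial procedures, and that severe illness and vital status continue to be collected through the existing phones, home visits and hospital records wherever valid consent exists and has not been withdrawn. The condition must cover invalid as well as withdrawn consent, since inadequate consent is one of the section's own examples.
2. **State how every infant enters the 14-week estimate.** Include all randomized infants by allocated arm in the 14-week risk ratio and risk difference, for example from cumulative incidence with censoring. Say whether the full-case default concerns outcomes, covariates or both.
3. **Add a sensitivity analysis for informative loss**, by multiple imputation or a tipping-point analysis. Cumulative incidence with censoring also assumes non-informative loss, so it does not replace step 1 or this check.
4. **Report removals** by arm, date and reason. The protocol already requires dates and reasons of deviations to be documented.

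The cost is a short change of wording, a few extra contacts or record checks, and some added analysis. The clinical decision on whether to remove a child is unchanged.

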## Plan of analysis

The data will be analyzed using Stata version 14 or later (StataCorp LP, TX, USA) and SAS version 9.2 or later. Continuous variables with right-skewed distributions will be log-transformed. Means with standard deviations will be used to summarize symmetrically distributed continuous variables while medians with interquartile ranges will be used for non-normally distributed continuous variables, and percentages for categorical variables. Between-group comparisons for continuous variables that are symmetrically distributed will be made using *t* tests or, if adjustment for other variables are required, linear regression, while Wilcoxon rank sum tests will be used to compare continuous variables where even their log-transformed values remains nonsymmetrically distributed. Group comparisons for categorical variables will use chi-square tests and regression with generalized linear models of the binomial family with a log link (“relative risk regression”) or logistic regression. We will use two-sided statistical tests and 95% confidence intervals for descriptive results, efficacy estimates and safety estimates. All relevant data; from both scheduled and unscheduled visits will be included in the analysis.

### Primary analysis

The main study outcomes are severe illness during the first 14 weeks of life and immunological parameters. Although the sample size estimations are based on specified relative risks, i.e., the occurrence of one or more illness episodes per child, our final analysis will also use incidence density and use Poisson regression or, in case of overdispersion, negative binomial regression analyses, to estimate incidence rate ratios (IRR), enabling us to capture more than one illness event in each child. Further, children who are lost to follow-up will be included in time-to-event analyses, censoring children during periods when data could not be recorded. All randomized children will be included in an *intention-to-treat* analysis.

To take into account multiple study events occurring in the same child, we will in the regression models utilize generalized estimating equations (GEE), as appropriate. The effect of the intervention on the occurrence of severe illness will be estimated using both relative (relative risks (RR), IRR and hazard ratios (HR)) and absolute (risk differences and incidence rate differences (IRD)) measures of effect. In the event that the “relative risk regression” model fails to converge, risk ratios will be obtained from logistic regression [70] or from a modified Poisson regression model with robust variance [71, 72].

Also, autoregressive correlation approaches will be used to account for multiple and possibly correlated observations within the same study participant. These methods take the correlation structures into account and thereby the fact that measurements taken closer in time for an individual are likely to be more correlated than two measurements taken farther apart for that same individual. Efficacy will be calculated as 100 × (1 − RR), 100 × (1 − IRR) or 100 × (1 − HR). The prevalence of BCG scarring will be compared between the two study arms using the abovementioned approaches, as appropriate. Linear regression and or *t* tests will be used to compare the TNF and IFN-γ responses between the trial arms. We will consider adjusting for potential confounders if: (1) there are baseline imbalances between trial arms, (2) the variables for which there are such baseline differences are strongly associated with the study event or (3) they cause a ≥5% difference in the effect measures when they are added to the main model. Full case analyses will be default, but appropriate imputations will be considered for missing data.

In addition to the *intention-to-treat analysis*, where outcomes will be compared according to the random allocation, *instrumental variable analyses* will be conducted in an attempt to estimate biological/causal effects of the actual receipt of the vaccine. In these analyses, random allocation will be the instrument. To enable such analyses, actual receipt as well as the age of BCG vaccination will be captured in all participants. We will also perform *per-protocol* and *as-treated* analyses.

The primary analyses will include all HIV-1-exposed infants, adjusting for any imbalance in HIV-1 status between the two trial arms, as appropriate. However, we will also perform an analysis of the large subgroup of babies who remain uninfected with HIV-1.

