## Methods/design

### Hypotheses

Compared to deferring BCG vaccination until 14 weeks of age, BCG administered within the first 24 h of birth leads to at least a 30% relative risk reduction of severe illness^1^ among HIV-1-exposed infantsDelayed BCG results in at least a 30% higher production of TNF, IL-1β, IL-6, IL-10, IL-17, IL-22 and IFN-γ in response to mycobacterial (from *Mycobacterium tuberculosis* and PPD) and non-mycobacterial (from *Escherichia coli, Candida albicans* and *Staphylococcus aureus*) antigens compared to when BCG is administered at birth in HIV-1-exposed infants

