### Primary objectives

To compareThe risk of severe illness in the first 14 weeks of life, andThe production of TNF, IL-1β, IL-6, IL-10, IL-17, IL-22 and IFN-γ in response to mycobacterial (from *M. tuberculosis* and PPD) and non-mycobacterial (from *E. coli, C. albicans and S. aureus*) antigens at birth (before BCG vaccination) and at 1, 14, 15 and 28 weeks of age among HIV-1-exposed infants administered BCG at birth with those administered a delayed BCG

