### Hypothesis B

The outcome for this hypothesis is the production of relevant cytokines in response to mycobacterial and non-mycobacterial antigens. Based on previous studies [33, 66] we expect that comparisons involving 50 children in each arm will be sufficient to detect biologically relevant differences.

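### Adjustment of the co-primary cytokine comparison for the pre-BCG birth value is left to data-dependent rules, and the sufficiency of 50 infants per arm is not tied to the hypothesised 30% difference.

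*Protocol article*

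**What the plan says.** - **Hypotheses (second hypothesis).** Delayed "BCG results in at least a 30% higher production of TNF, IL-1β, IL-6, IL-10, IL-17, IL-22 and IFN-γ in response to mycobacterial" and non-mycobacterial antigens.
- **Primary objectives.** Responses are to be compared for "antigens at birth (before BCG vaccination) and at 1, 14, 15 and 28 weeks of age", so a pre-vaccination value is part of the objective.
- **Primary outcome measures.** TNF, IL-1β, IL-6 and IFN-γ at 1, 14, 15 and 28 weeks. Birth is not listed.
- **Functional immunology assessment.** Stimulation with the nonspecific stimuli is scheduled at 1, 15 and 28 weeks. Neither birth nor week 14 is listed.
- **Hypothesis B (trial size).** Citing previous studies, "we expect that comparisons involving 50 children in each arm will be sufficient to detect biologically relevant differences". No SD, power, significance level or target difference is given.
- **Plan of analysis.** "Continuous variables with right-skewed distributions will be log-transformed". Symmetric variables are compared by t test, or by linear regression where adjustment is required; the Wilcoxon test covers variables that stay asymmetric after log transformation.
- **Primary analysis.** Linear regression and/or "tests will be used to compare the TNF and IFN-γ responses between the trial arms". Adjustment for potential confounders is considered if there is baseline imbalance, if the imbalanced variables are strongly associated with the study event, or if adding them changes the effect measure by 5% or more.
- **Randomization.** Stratified by clinic.

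**The concern.** Two things are fixed badly for the smallest sample in the trial.

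First, the adjustment rule answers the wrong question for a baseline measurement of the outcome. In a randomised comparison the main reason to adjust for such a value is precision, and that gain does not depend on imbalance. The stated criteria look for chance confounding and are judged after the data are seen. A strongly prognostic but well-balanced birth value meets none of them. Whether it enters the model, and hence which estimate is reported, would depend on the data.

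Second, the trial states a 30% target difference and a sample size of 50 per arm, and nothing connects them. A reader of a null result could take the word sufficient to mean that a 30% difference had been ruled out. Nothing in the protocol shows that it could be.

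**Working it through.** **Reproducing the plan's figure.** The 50 per arm cannot be reproduced, because Hypothesis B gives no inputs. By contrast, the 1914 for Hypothesis A does reproduce from 15% versus 10%, 90% power, two-sided 0.05 and a continuity correction. The 50 is therefore inverted: what does it detect?

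**Inputs.**
- n = 50 per arm (Hypothesis B), 1:1 (Randomization), all evaluable (assumed).
- Two-sided tests: "We will use two-sided statistical tests and 95% confidence intervals for descriptive results, efficacy estimates and safety estimates". The 0.05 level is stated only for Hypothesis A ("Two-sided significance level 0.05") and is assumed here.
- Target ratio 1.30 (Hypotheses); log scale from the transformation rule: ln(1.30) = 0.262.
- Power: not stated for this outcome; 80% and 90% are both shown.
- Log-scale SD and correlation of birth with later value: not stated; ranges are assumed.

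**Detectable difference.** Normal approximation: (z for alpha + z for power) × √(2/50).
- 80%: (1.960 + 0.842) × 0.2 = 0.560 SD; noncentral t with 98 df: 0.566 SD.
- 90%: (1.960 + 1.282) × 0.2 = 0.648 SD; noncentral t: 0.655 SD.

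**Largest log-SD at which a 30% difference is detectable.** 0.262 / detectable difference.
- 80%: 0.464 (t), 0.468 (normal).
- 90%: 0.401 (t), 0.405 (normal).
- With 45 evaluable per arm (the 10% attrition that the protocol applies only to Hypothesis A): 0.44 and 0.38.

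**Power for a 30% difference, 50 per arm, unadjusted (t).**

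| Assumed log-SD | Power |
|---|---|
| 0.4 | 90% |
| 0.5 | 74% |
| 0.6 | 58% |
| 0.8 | 37% |
| 1.0 | 25% |

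**Gain from the birth value.** Residual variance is multiplied by 1 − r², so the equivalent n is 50 / (1 − r²).

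| Assumed r | Variance factor | Equivalent n per arm |
|---|---|---|
| 0.1 | 0.99 | 50.5 |
| 0.3 | 0.91 | 55 |
| 0.5 | 0.75 | 67 |
| 0.6 | 0.64 | 78 |

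At r = 0.5, power for a 30% difference (normal approximation) rises from 59% to 71% at SD 0.6, and from 26% to 33% at SD 1.0. Adjustment helps, but does not rescue 50 per arm if the SD is large.

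**The case against.** The strongest reply is that the protocol does not exclude the birth value. Linear regression is named, conditional adjustment is allowed, autoregressive methods are planned for repeated observations, and the choice of covariate is often left to an analysis plan. This stands in part: a reader might infer that the plan forbids or ignores the birth value, and the text does not support that. But the protocol is not silent. It states a rule for adjustment, and that rule is the weaker choice for this covariate.

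A second reply is that the birth assay may not exist. Only the Primary objectives list it, while Postnatal screening describes cord blood for a full blood count with a sample stored for future work. This stands, and makes the fix conditional.

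Third, the gain is speculative. The Background says that many early immune anomalies in these infants are transient, so a birth value may predict later responses poorly. This stands too: the correlation is unknown and the gain could be close to nil.

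Fourth, a reader might infer that 50 per arm is too small. No SD is given, and nothing in the documents shows that 0.46 is low or high for these assays, so that inference is not supported.

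Finally, naming only TNF and IFN-γ might suggest that IL-1β and IL-6 have no method. The general rule for continuous variables largely covers them, so this is a drafting inconsistency.

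**Conclusion.** The concern holds in a limited form. The unadjusted randomised comparison is valid. The weakness is that use of a listed pre-vaccination value is decided by data-dependent rules that overlook precision. The potential gain is equivalent to 5 to 28 more infants per arm at assumed correlations of 0.3 to 0.6, and close to zero at 0.1; it exists only if the birth assay is run.

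The sufficiency statement is unsupported for the hypothesised 30% difference. With 50 evaluable per arm at two-sided 0.05, and no multiplicity adjustment, it holds only if the log-scale SD is at most about 0.46 (80% power) or 0.40 (90%). These limits assume analysis on the log scale; attrition or a multiplicity correction would tighten them.

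**What to change.** 1. In Primary analysis, pre-specify for TNF, IL-1β, IL-6 and IFN-γ a linear regression of the log response, at each age after birth, on arm, clinic (the randomisation stratifier) and the same infant's log birth value for that cytokine-antigen pair. Report the ratio of geometric means with its 95% confidence interval. Exempt these covariates from the imbalance and change-in-estimate rules.
2. Reconcile the Primary objectives with the Primary outcome measures and the Functional immunology assessment on whether stimulation is run at birth. If it is not, adjust for clinic only.
3. Keep the birth value as the covariate in both arms. A week-14 value in the delayed arm would be post-randomisation and measured at a different age from the other arm's covariate, so the adjusted contrast would lose its randomised interpretation.
4. In Hypothesis B, replace the sufficiency statement with the detectable difference (0.57 SD at 80% power, 0.65 SD at 90%) and the log-SD that a 30% difference requires. If the cited studies provide an SD, state it.

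The cost is wording only, with no extra samples if the birth stimulation is run as the objectives say. The substudy's stated sensitivity may look less favourable.
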